#### Psychological processes and alcohol-related parameters

The difference between both treatment arms with respect to change from baseline to one week post-psilocybin administration, as well as four weeks, three and six months posthospital discharge on the following scales:

The Acceptance and Action Questionnaire II (AAQII; [110]) to assess the construct of psychological (in)flexibility.The Multidimensional Assessment of Interoceptive Awareness (MAIA; [111]) to evaluate interoceptive processes across 8 dimensions: noticing, trusting, not distracting, not worrying, attention regulation, emotional awareness, self-regulation, and body listening.The Watts Connectedness Scale (WCS; [63]) to measure felt connectedness to self, others, and the world.The Penn Alcohol Craving Scale (PACS; [112]) to assess the frequency, intensity, and duration of past-week cravings.The Alcohol Abstinence Self-Efficacy Scale (AASE; [113]) to evaluate participants’ confidence in their ability to resist drinking alcohol in high-risk situations.Readiness to change alcohol consumption behavior will be measured by collecting Likert-scale ratings of the participants’ (1) perception of the importance of change in drinking; (2) confidence in their ability to change; (3) readiness for change and (4) commitment to the goal of abstinence [15].

#### Expectancy, blinding, and therapeutic alliance

Participants’ expectancy will be assessed with the Stanford Expectations of Treatment Scale (SETS; [114]) at baseline, and blinding efficacy will be assessed by asking participants and therapists to guess group allocation and indicate guess certainty following the psilocybin administration session. Furthermore, we will assess therapeutic alliance in both participants and therapists after the last preparation session with the Working Alliance Inventory-Short Revised (WAI-SR; [115]).

**Table 1 Tab1:** Schedule of key study activities

	Screening	Baseline	Preparation 1	Preparation 2	Dosing	Integration 1	Integration 2	4-week endpoint	6-month follow-up
**Days relative to dosing**		-20	-7	-1	0	+ 1	+ 7	+ 35	+ 190
**Key assessments**									
Informed consent	X								
Psychiatric screening	X								
Physical screening	X								
**Key outcomes**									
*Clinical outcomes*									
Heavy drinking		X						X	X
Drinking days		X						X	X
Abstinence		X						X	X
PEth								X	
Mood		X		X			X	X	X
Anxiety		X		X			X	X	X
Trauma		X		X			X	X	X
Global functioning		X						X	X
*Safety*									
Adverse events		X	X	X	X	X	X	X	X
*Feasibility*									
Insclusion rates	X								
Retention rates			X	X	X	X	X	X	X
*Neurocog. outcomes*									
Neuroplasticity (LTP)			X			X	X		
Cue reactivity			X			X	X		
Inhibition			X			X	X		
*Drug experience*									
Mystical (MEQ)					X				
Acceptance/Avoidance (APEQ)					X				
Trauma access/process. (Helioscope Q.)					X				
*Psychological processes*									
Flexibility (AAQQ II)		X		X			X	X	X
Interoception (MAIA)		X		X			X	X	X
Connectedness (WCS)		X		X			X	X	X
*Alcohol-related parameters*									
Craving (PACS)		X		X			X	X	X
Abstinence self-efficacy (AASE)		X		X			X	X	X
Readiness to change		X		X			X	X	X

*Abbreviations: PEth* Phosphatidylethanol, *LTP* Long-term potentiation, *MEQ* Mystical Experience Scale, *APEQ* Acceptance/Avoidance-Promoting Experiences Questionnaire, *AAQ-II* Acceptance and Action Questionnaire Version 2, *MAIA* Multidimensional Assessment of Interoceptive Awareness, *WCS* Watts Connectedness Scale, *PACS* Penn Alcohol Craving Scale, *AASE* Alcohol Abstinence Self-Efficacy Scale

### Recruitment

The primary source of participants will consist of individuals who attend a preadmission consultation to enroll in the inpatient alcohol detoxification program at the Brugmann University Hospital. The study protocol will be presented to these patients, who may then attend a screening visit (eligibility screening 1) with an investigator and a therapist after signing the informed consent form.

Additional recruitment venues will consist of referrals from local inpatient and outpatient psychiatric units and local and national referrals from physicians.

### Data analysis

The data will be analyzed according to a statistical analysis plan that will be uploaded on ClinicalTrials.gov before unmasking. Significance levels for all analyses will be set at 0.05. Clinical outcome analyses (alcohol consumption parameters) will be performed on the intention-to-treat population, including all randomized patients who have completed the dosing session (visit 7). Changes in continuous outcomes will be analyzed with mixed-model analysis of variance with Helmert contrasts when indicated. For time series analysis, general linear mixed models will be used in the case of missing data. Mediation analyses will be used to evaluate whether hypothesized mechanistic variables mediate the effect of treatment on clinical improvements, for example, whether the mystical experience score during psilocybin administration mediates the impact of treatment on changes in the percentage of heavy drinking days. Treatment-emergent adverse events will be classified, tabulated, and treatment groups contrasted using Chi squared or Fisher’s exact test.

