#### Dose rationale

The optimal therapeutic dose of psilocybin in the treatment of sAUD has not been determined. While in the only published contemporary RCT of PAT for AUD, a second dose of up to 40 mg/70 kg was administered (following a first dose of 25 mg/70 kg, [15]), all currently ongoing trials in this population have opted for one to two doses of 25 mg (NCT04141501, NCT05416229, NCT05646303, NCT04620759, and NCT04410913). Of note, relative doses have been mostly substituted with absolute doses, following evidence that body weight has no influence on psilocybin pharmacokinetics [71] and subjective effects [72] in humans. There may be some advantages to selecting a higher dose of 30 mg. First, preclinical evidence suggests a dose-dependent effect on increases in the expression of some neuroplasticity-related genes induced by serotonergic psychedelics [73–75], a key proposed therapeutic mechanism [44, 45]. Second, phase I and II studies suggest a dose-dependent effect on the quality of the psychedelic experience [54, 76], with high mystical experience scores associated with 30 mg/70 kg of psilocybin [76], another proposed therapeutic mechanism [77]. Last, early studies with LSD and contemporary studies with psilocybin suggest that patients with AUD may tend to display more tolerance to serotonergic psychedelics, whereas high doses of 30–40 mg/70 kg are well tolerated in this population [15, 54, 78].

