#### Benzodiazepine discontinuation

Benzodiazepines with a short half-life (lorazepam [79]) will be used for the treatment of acute alcohol withdrawal syndrome upon admission in the inpatient alcohol detoxification program. The shorter half-life allows us to minimize the potential benzodiazepine-psilocybin interaction by ensuring a relatively lower lorazepam plasma concentration rapidly after full tapering off (at least 3 days before psilocybin administration), which is relevant, as benzodiazepines might blunt the psychedelic experience. The Clinical Institute Withdrawal Assessment Alcohol Scale Revised (CIWA-AR; [80]) will be used to assess withdrawal symptoms to ensure safe progressive lorazepam discontinuation, in line with evidence-based practice guidelines recommending individualized tapering off schedules with withdrawal scales [81]. In case full tapering off from lorazepam cannot be achieved within 17 days due to withdrawal symptoms, participants will be excluded from the study.

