#### Psilocybin dosing session

Psilocybin will be administered in a specifically dedicated room in the Brugmann University Hospital, decorated in a way that creates a warm and home-like atmosphere rather than a sterile clinical setting, thereby maximizing participant comfort [9]. The psilocybin session will be video-recorded for training (supervision) and safety purposes.

Participants will be dosed per os and receive either a high dose of psilocybin (30 mg) or a low dose of psilocybin (5 mg - active placebo) as determined by computer-generated randomization. They will be invited to lie comfortably on a bed, wearing eyeshades and headphones, and instructed to direct their attention toward their internal experience and ‘trust, let go, be open’ [90]. Through headphones, participants will be listening to a standardized music playlist, specifically curated to accompany the three principal intensity phases of the experience: the onset of psychoactive effects, the peak plateau, and the return to an ordinary state of consciousness [91].

After psilocybin administration, participants will remain under observation for 6–8 h, based on the drug’s duration of action [92]. Vital signs will be measured at 30 min intervals for the first 2 h and every hour thereafter until session completion. The assigned therapist-dyad will remain present throughout, and interactions with the participants will be supportive and nondirective.

Psychedelics generally intensify emotional experience and may give rise to anxiety, dysphoria, fear, panic, or paranoia [9]. Across PAT trials, the first response to psychological distress has been psychological support and reassurance, as well as therapeutic touch such as hand holding, according to preestablished individual boundaries. Participants may also be redirected to other grounding techniques practiced during the preparation sessions, namely, body scan and diaphragmatic breathing. Psychological support has generally been sufficient to address transient psychological distress across contemporary trials [13, 15, 35]. However, if insufficient, rescue medication will be available for one-time administration to treat anxiety [Temesta Expidet^TM^ (Lorazepam) 1-2.5 mg, sublingual] and acute psychosis posing a danger to the participant or others [Zyprexa Velotab^TM^ (Olanzapine) 5–10 mg sublingual]. Hypertensive urgency will be treated with captopril, 25–100 mg per os. Emergency treatment will be available on site.

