### Outcomes

#### Primary clinical outcome

The primary clinical outcome is the difference between the two treatment arms in terms of change from baseline (8 weeks to 1 day pre-enrollment) to 4 weeks posthospital discharge (1 day to 4 weeks postdischarge) in the percentage of heavy drinking days, defined as ≥ 5 standard drinks/60 g of alcohol for males and ≥ 4 standard drinks/48 g of alcohol for females [15]. A reduction in heavy drinking days yields clinically significant health ameliorations [94], matches the treatment objectives of numerous patients [95] and is recognized by the European Medicines Agency as an adequate measure of efficacy [96]. Moreover, previous results suggest that PAT might lead to a decrease in alcohol consumption without necessarily inducing complete abstinence [15, 54]. We opted for a primary clinical outcome measure at four weeks posthospital discharge to limit attrition, as well as because the literature suggests that at least 50% of patients resume excessive heavy drinking within the first month following an inpatient detoxification program [3, 97]. Longer term follow-up data will be collected up to six months posthospital discharge (see secondary outcomes). The TLFB [68] will be used to measure alcohol consumption. The TLFB is a semi-structured interview designed to assess daily alcohol (and other drug) use by obtaining estimates of quantity, frequency, and usage patterns within a specific timeframe. The tool has demonstrated adequate to excellent reliability and validity [98, 99]. See Table 1 for an overview of key outcomes and sampling time points.

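### The set called intention-to-treat is limited to patients who completed the dosing session, a post-dose event, so the primary comparison could be biased if non-completion differs by arm

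*Protocol article*

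**What the plan says.** The rule stands in the Data analysis section of the protocol article. It covers "Clinical outcome analyses (alcohol consumption parameters"), which are to be "performed on the intention-to-treat population, including all randomized patients who have completed the dosing session (visit 7"). The Primary clinical outcome section makes the percentage of heavy drinking days the primary measure: "The primary clinical outcome is the difference between the two treatment arms in terms of change from baseline" to four weeks after discharge. The primary comparison therefore falls under the rule.

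The Psilocybin dosing session section shows what completing that visit involves. Participants "receive either a high dose of psilocybin (30 mg) or a low dose of psilocybin (5 mg - active placebo) as determined by computer-generated randomization". The visit then continues: "After psilocybin administration, participants will remain under observation for 6–8 h". The same section warns that "Psychedelics generally intensify emotional experience and may give rise to anxiety, dysphoria, fear, panic, or paranoia" and provides rescue medication for anxiety and acute psychosis and treatment for hypertensive urgency. The Dose rationale section adds that "phase I and II studies suggest a dose-dependent effect on the quality of the psychedelic experience".

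The article describes no analysis of all randomized patients and does not say how randomized patients who do not complete the session are handled.

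**The concern.** Intention-to-treat means that everyone randomized is analysed in the arm assigned. The set described here depends on an event that occurs hours after the randomized treatment starts to act. The label and the definition disagree, and a reader of the results would take the analysis for something it is not.

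Randomization balances the arms at allocation. If the dose affects who finishes the session, the patients left in each arm need no longer be comparable. The rest of the plan does not repair this. The 25% attrition allowance and the continued inclusion until 46 patients complete visit 14 protect power. The mixed models for missing data cannot help either, because excluded patients never enter the model. All alcohol-consumption outcomes are affected, the primary one included.

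The statistical analysis plan is still to be posted, but this is not a detail left open for it. The article fixes the rule.

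**Working it through.** **1. The plan's own figure.** Inputs from the Sample size section: Cohen's f = 0.25, power 0.9, type I error 0.05, two groups, two timepoints (m = 2), 46 evaluable, 25% attrition, 62 in total. The correlation rho between timepoints is not given; rho = 0.5 is assumed here.

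- Group-by-time interaction: noncentrality = f² × N × m / (1 − rho), with 1 and N − 2 degrees of freedom.
- N = 46: 0.0625 × 46 × 2 / 0.5 = 11.5, power 0.912. N = 44 gives 0.8997, just short of 0.9. So N = 46 is reproduced.
- Other correlations give N = 88 (rho = 0), 62 (rho = 0.3) and 28 (rho = 0.7).
- Attrition: 46 / 0.75 = 61.3, rounded up to 62, or 31 per arm.

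The sample size does not depend on the population rule. If all 62 were analysed with outcome data, power at the same f and rho would be 0.972.

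**2. Order of events.** Randomized dose swallowed, then 6–8 h of observation, then session completed. The acute effects in between are described as dose-dependent. Membership of the set is thus settled after the treatment has begun to act.

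**3. Form of the bias.** Suppose x of 31 high-dose patients and no controls are excluded, and the excluded patients' change is worse than the completers' by D, in SD units of the change score. The mean of all 31 is the completers' mean worsened by (x/31) × D. Analysing completers only therefore shifts the comparison by

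bias = (x/31) × D.

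More generally, the bias is the difference between the arms in (excluded share × D). It vanishes if that product is the same in both arms, and it changes sign if the excluded patients would have done better.

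**4. Illustration.** Neither x nor D is in the documents; both are assumed. The type I error is that of a two-sided t test on the change score, (31 − x) against 31 patients, when the all-randomized means are equal. The noncentrality is bias / √(1/(31 − x) + 1/31), and no other data are missing.

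| x | D | bias (SD) | noncentrality | type I error |
|---|---|---|---|---|
| 1 | 1 | 1/31 = 0.032 | 0.032/0.256 = 0.13 | 0.052 |
| 2 | 1 | 2/31 = 0.065 | 0.065/0.258 = 0.25 | 0.057 |
| 3 | 1 | 3/31 = 0.097 | 0.097/0.261 = 0.37 | 0.065 |

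Varying D for x = 1 to 3: D = 0.5 gives 0.016 to 0.048 SD (type I error 0.050 to 0.054), and D = 1.5 gives 0.048 to 0.145 SD (0.054 to 0.085). A more extreme case, x = 5 with D = 1, gives 0.161 SD and 0.092.

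**The case against.** The strongest reply is that almost everyone who is dosed will complete the visit. It is a single oral dose given to supervised inpatients with two therapists present throughout. Distress, psychosis and hypertensive urgency are managed on site, and nothing says that such a reaction or rescue medication ends the session or removes a patient from the analysis. The article also reports that psychological support has usually sufficed in earlier trials and that high doses have been well tolerated in this population. The authors may simply have meant patients who received the drug. Exclusions would also be visible in the planned CONSORT diagram and retention figures, and the rule is stated only for the alcohol-consumption analyses, not for safety.

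Most of this stands, and it limits the likely size of the problem. It does not make the definition right: the text says *completed*, and showing exclusions in a flow diagram does not put the patients back into the analysis.

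Three stronger readings are tempting, and the documents do not support them.

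- *That exclusions would fall mostly in the 30 mg arm.* Dose-dependent effects make this possible, but the article gives no rate and does not say that sessions are cut short more often at the higher dose.
- *That the bias would favour the high dose.* The background on psychological mechanisms cites hypotheses in which access to otherwise unbearable memories, or learning to let go, contributes to benefit. Removing strong reactors could then work against the high dose.
- *That losses before dosing add to the bias.* The article says of the lorazepam taper: "In case full tapering off from lorazepam cannot be achieved within 17 days due to withdrawal symptoms, participants will be excluded from the study". This precedes intake, so the dose cannot cause it, and losses before intake under blinding are largely independent of arm. The article does not state when randomization takes place, so nothing can be concluded about the timing of allocation.

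**Conclusion.** The point holds in a limited form. The set is mislabelled: as written it consists of patients who completed dosing, and following the rule literally would drop dosed patients from a comparison reported as intention-to-treat. That much rests on the text alone.

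Whether material bias follows is uncertain. It requires non-completion, or the prognosis of non-completers, to differ by arm. With 1 to 3 exclusions, all in one arm and all 1 SD worse than completers, the shift is about 0.03 to 0.10 SD and the two-sided type I error rises from 0.05 to about 0.052 to 0.065. These are assumed inputs, not estimates. If non-completion is rare or alike in both arms, the effect is negligible. The direction is unknown.

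**What to change.** Before unmasking, amend the Data analysis rule, and carry it into the statistical analysis plan, in one of two ways.

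1. Preferred: make the primary set all randomized participants, analysed in the arm assigned, and continue to seek TLFB data from those who do not complete dosing.
2. If a modified set is kept: label it modified intention-to-treat, define it as randomized and received any study drug, without requiring completion of the session, and add a sensitivity analysis of all randomized participants.

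The cost is a sentence or two of text, follow-up interviews with what may be very few patients and, under the second option, one more analysis. The targets of 46 evaluable and 62 in total stay as they are.

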#### Sample size

In line with extant studies indicating medium to large effects of PAT on alcohol consumption in patients with AUD (Cohen’s d = 1, [54]; Hedges’ g = 0.52 [15]), the sample size was calculated to observe a medium-size effect (Cohen’s f = 0.25) with a power of 0.9 and a type I error set at 0.05. A priori power calculation based on the primary clinical hypothesis (mixed-design analysis of variance, two groups: high dose vs. active placebo; two timepoints: % heavy drinking days from 8 weeks prehospitalization to 1 day prehospitalization vs. % heavy drinking days from hospital discharge to 4 weeks posthospital discharge) indicated a needed sample size of *n* = 46. Accounting for 25% attrition, we set the total sample size to *n* = 62. If the drop-out rate is higher, we will continue to include participants until 46 have completed visit 14 (primary clinical outcome).

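### The two-timepoint ANOVA planned for the primary outcome is a change-score test: valid, but less precise than adjusting for the baseline already collected, and its handling of missing 4-week data is unclear

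*Protocol article*

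**What the plan says.** The Primary clinical outcome section defines the outcome as the between-arm difference in change in percentage of heavy drinking days, from the weeks before enrolment to four weeks after discharge. Sample size powers this as a "mixed-design analysis of variance, two groups: high dose vs. active placebo; two timepoints", with f = 0.25, "with a power of 0.9 and a type I error set at 0.05". The calculation "indicated a needed sample size of *n* = 46". "Accounting for 25% attrition", the total becomes 62, and recruitment continues if needed until 46 participants have completed the primary visit.

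Data analysis then says: "Changes in continuous outcomes will be analyzed with mixed-model analysis of variance". It names no baseline covariate. On missing values it adds: "For time series analysis, general linear mixed models will be used in the case of missing data". The analysis set is called intention-to-treat but is limited to randomised patients who completed the dosing session. The section refers to a statistical analysis plan, not shown, to be posted before unmasking.

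**The concern.** Two things are at stake.

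**Precision.** With two arms and two timepoints, the group-by-time interaction compares mean change between arms. A change score subtracts the whole baseline value whether or not follow-up tracks baseline that closely. When the correlation is weak, this adds baseline noise to the outcome. Here baseline is drinking before admission and follow-up is drinking after a four-week inpatient programme, so a modest correlation is plausible, although the protocol gives no figure. Loss of precision matters in a trial sized on 46 completers.

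**Missing data.** A classical two-timepoint ANOVA needs both values. The mixed-model sentence is limited to time series and applies only if data are missing. It is not clear that it covers the two-period primary comparison, and the condition makes the choice of model depend on the data observed.

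**Working it through.** **Inputs.** From Sample size: f = 0.25, α = 0.05, power 0.90, 46 evaluable, 25% attrition. The design is 1:1. The correlation ρ between the two periods and the SDs are not stated, so they are treated as assumptions and varied.

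**1. Reproduce the plan's figures.** For the within-between interaction, the noncentrality is λ = f²·N·m/(1−ρ), with m = 2 and 1 and N−2 df.
- At ρ = 0.5 and N = 46, λ = 0.0625 × 46 × 2 / 0.5 = 11.5 and power is 0.9125. N = 44 gives 0.8997, so 46 is reproduced.
- Other correlations do not reproduce it: ρ = 0 needs 88, ρ = 0.3 needs 62, ρ = 0.7 needs 28.
- Attrition: 46/0.75 = 61.3, rounded up to an even 62.

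**2. Show that the test is a change-score t-test.** In this formula f = δ/(4σ), so f = 0.25 is a difference in change of δ = 1.0σ. The change-score SD at ρ = 0.5 is σ√(2(1−0.5)) = σ. The t noncentrality is 1/√(4/46) = 3.391, and 3.391² = 11.5, the same λ. Power is again 0.9125.

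**3. Compare with baseline adjustment, equal SDs.** In units of σ², the change-score variance is 2(1−ρ) and the baseline-adjusted variance is 1−ρ². Their ratio, adjusted over change, is (1+ρ)/2. Power is for δ = 1σ and N = 46, with 44 df (change) and 43 df (adjusted).

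| ρ | Change variance | Adjusted variance | Ratio | Power, change | Power, adjusted |
|---|---|---|---|---|---|
| 0.2 | 1.60 | 0.96 | 0.60 | 74.6% | 92.3% |
| 0.3 | 1.40 | 0.91 | 0.65 | 80.0% | 93.5% |
| 0.5 | 1.00 | 0.75 | 0.75 | 91.2% | 96.9% |
| 0.7 | 0.60 | 0.51 | 0.85 | 99.0% | 99.6% |

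**4. Unequal SDs.** Let r be follow-up SD over baseline SD, with baseline SD 1. Change variance is 1 + r² − 2ρr and adjusted variance is r²(1−ρ²). The difference is (1−ρr)², which is never negative, so adjustment costs at most one degree of freedom.
- r = 1.5: ratio 0.815 at ρ = 0.2 and 0.964 at ρ = 0.5.
- r = 2: ratio 3.84/4.20 = 0.914 at ρ = 0.2, 3.64/3.80 = 0.958 at ρ = 0.3, and 3.00/3.00 = 1.00 at ρ = 0.5.
- A simulation with zero-inflated percentages (baseline SD about 0.18, follow-up SD about 0.33, ρ about 0.25) gave power 0.36 for change and 0.38 adjusted, with type I error about 0.05 for both.

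**5. Missing follow-up.** 20,000 simulated trials, N = 62, about 25% missing, ρ = 0.5, true effect −1.00.
- Missing completely at random: SD of the estimate 0.296 for the completer change score, 0.287 for an unconstrained likelihood model, 0.260 for the baseline-adjusted model.
- Missingness depending on baseline in opposite directions in the two arms, a deliberately strong case: the completer change score averaged −0.79. The adjusted and likelihood models averaged −1.00.
- With one follow-up period, ANCOVA on completers and the constrained-baseline likelihood model give the same estimate.

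**The case against.** The strongest reply is that nothing here is wrong. Outcome, power calculation and test agree with one another, and a change-score comparison holds its type I error under randomisation. Covariates and missing-data handling are often settled in the analysis plan. The large gains assume equal SDs and a correlation that the protocol does not give, and the zero-inflated simulation shows only two percentage points of power.

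Most of that stands. This is an improvement, not an error, and its size is uncertain. It is still more than absent detail, because the article itself fixes the ANOVA, and adjustment is not materially worse in any of these settings.

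Four stronger readings are tempting, and the document does not support them.
- **The primary test uses completers only.** This is inferred. Heavy drinking is also measured at six months, so the mixed-model sentence may be meant to cover it. The wording is ambiguous, no more.
- **A likelihood model would secure the intention-to-treat claim.** The analysis set leaves out randomised patients who did not complete dosing. That is a separate matter of population, which a choice of model does not settle.
- **About 16 of 62 participants (62 − 46) would be lost and could be recovered.** Sixteen is an upper bound: some attrition may precede dosing, for example under the lorazepam tapering exclusion, and so fall outside the analysis set. With a single follow-up, those who lack it add almost nothing to the estimate. The rule to recruit until 46 complete also protects the planned count.
- **The adjusted model corrects dropout caused by relapse.** That would be missing not at random. The simulation above covers missingness that depends on baseline and arm only.

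**Conclusion.** The point holds as a worthwhile improvement. The planned primary test equals a change-score t-test, and adjustment for baseline is at least as precise apart from one degree of freedom. At equal SDs the variance falls by 40%, 35% and 25% at ρ = 0.2, 0.3 and 0.5. The last is the correlation that the stated 46 implies. With a follow-up SD twice the baseline SD, the reduction is about 9% at ρ = 0.2, 4% at ρ = 0.3 and nil at ρ = 0.5. Adjustment also removes bias from missingness that depends on baseline and arm, provided data are missing at random given these.

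The gain is not a reason to recruit fewer. The planned effect corresponds to a full SD of difference in change. If the cited g = 0.52 is read on that scale, with ρ = 0.5 and equal SDs, power at 46 is about 41% for the change score and 51% adjusted.

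Whether the mixed-model sentence applies to the primary comparison remains open on the text and needs to be stated.

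**What to change.** Before unmasking, name one baseline-adjusted model as the primary analysis, whether or not data are missing. Either of these would serve:
- a linear mixed model for baseline, 4 weeks and 6 months, with baseline means constrained equal across arms; or
- ANCOVA on the 4-week percentage of heavy drinking days with baseline as covariate.

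The arm contrast at 4 weeks is primary in both. They are not interchangeable once 4-week values are missing: only the mixed model uses the 6-month value of a participant who missed the 4-week visit. Add one sensitivity analysis that counts unobserved days as heavy drinking days. State explicitly that the conditional mixed-model sentence does not govern the primary comparison. Keep the sample size as it is.

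The cost is a few sentences in the analysis plan and slightly more programming. No extra data are needed.
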